## Abstract

**Background:**

Excessive exposure to solar ultraviolet (UV) radiation can cause skin cancer. Implementing new technologies and computational algorithms can potentially change the outlook for cancer prevention and facilitate early detection of melanoma, thereby reducing mortality. Mobile technology as a potential provider of health services in delivering health information and conducting interventions, especially in skin fields, where a significant part of diagnosis is based on visual examination, can be important. Evidence showed that constructs of protection motivation theory (PMT) were good predictors of practicing sun protection behaviors in students. This study will investigate whether mobile applications improve safe and healthy behaviors and affect students' reduced UV exposure.

**Method/design:**

This randomized controlled trial will be conducted on 320 students on 06/04/2022 in Zahedan. We created mobile applications (Sunshine and Skin Health and WhatsApp apps). Sunshine and Skin Health app allows users to see their changed faces in three stages of adolescence, middle age, and old age based on sun protection behavior. The WhatsApp app has 27 health messages based on PMT theory, eight educational files, and a skin cancer clip that will be sent through WhatsApp during a week. Randomization will be performed using a 1:1 (control: intervention) ratio. The primary endpoint is the group difference in sun-protective behaviors and PMT constructs immediately after the intervention. The secondary endpoint is the group difference in sun-protective behaviors and PMT constructs at a 3-month follow-up. The data will be analyzed in SPSS.22, and the significance level will be considered at 0.05.

**Discussion:**

The present study examines the effectiveness of mobile applications in improving sun-protective behaviors. If this intervention enhances sun protection behaviors, it can prevent students’ skin damage.

**Trial registration:**

Iranian Registry of Clinical Trials IRCT20200924048825N1. Prospectively registered on 8 February 2021.

## Background and rationale

Sunlight exposure can be beneficial and harmful to health [1]. Long-term and continuous contact exposure to ultraviolet (UV) and recurrent sunburn, especially in the early years of life, increases the risk of skin cancer (especially melanoma and basal cell carcinoma), macular degeneration, and cataracts [2, 3]. Studies show that a significant proportion of skin cancer cases are due to excessive UV exposure [4, 5]. Skin cancer is one of the most serious public health problems and is the most common type of cancer in people with fair skin in many parts of the world [6]. Evidence from Iran has shown that due to high sunlight in most seasons and lack of proper coverage like outdoor clothing and hats, skin cancer has been increasing in recent years [7]. The annual UV index average map in Iran shows a very high index in the country’s southern half. The highest levels were observed in the southern states, especially in Sistan and Balochistan. This reflects the growing vulnerability of residents in these areas [8]. The most important foundation for preventing skin cancer is properly managing UV exposure to reduce or even prevent chronic sun damage, especially skin aging and skin cancer [9]. The following behaviors can reduce the damage caused by sunlight: shadow search, wearing appropriate sunscreen (including a wide-brimmed hat, matte UV sunglasses, and long-sleeve shirts), less exposure or no exposure to sunlight during peak hours (10 am to 4 pm), use sunscreen with SPF 30 or higher in areas without skin coverage, and avoid artificial sources of UV rays (fluorescent lamps, etc.) [10–12].

Over the last two decades, Mobile Health has provided health services exponentially through mobile phones and their applications [13]. In other words, healthcare providers use mobile technologies such as short message services (SMS) and mobile apps to provide health information and interventions [14]. Apps are software applications created to run a computer or mobile device to achieve a specific goal [15]; they can access remote databases, track time/place, and integrate user input to provide appropriate health information [16]. These apps are most important in skin care programs, where many diagnostics and follow-ups are based on visual examinations [17]. Implementing new technologies and computational algorithms can potentially change the outlook for cancer prevention and early detection of melanoma, consequently reducing the disease-specific mortality rate [18]. The increasing use of mobile phones is projected to reach more than six billion subscribers by 2021, which can be integrated into people’s daily lives to render health services to many people [19]. Today, the use of technology-based interventions is growing, such as the use of mobile applications [16], mails [20], and the use of SMS reminders (SMS text messages) for short message services [21, 22]. Facial aging interventions that change the user’s image and predict future appearance can motivate healthier behavior in the prevention of obesity, skin cancer, and smoking cessation. Preliminary results can be explained by the importance of the emergence of self-concept, especially in adolescence [23]. A systematic review of the interventions to promote sun protection behaviors in recreational settings showed poor and heterogeneous findings on the effectiveness of interventions. Consequently, it may be hypothesized that interventions over supportive social norms, which provide appearance-based information about skin aging photos (showing UV-damaged skin photos), are more effective than interventions on sun protection behaviors. Evidence indicates that using mobile technologies to promote health-related behaviors may be considered a new topic and a practical way to reach the target population [24]. Young people are increasingly moving away from traditional media such as newspapers and television and favoring web-based streaming. Web-based media has challenged the healthcare sector by creating new ways to reach young people with targeted personal advertising messages [25].

### Theory-based intervention to improve sun protection behavior

Theories of social cognitive, planned behavior, and protection motivation in the field of behavior change provide useful insights to explain variables influencing the adoption of sun protection behaviors [23]. PMT was proposed by Rogers [26] based on the value expectation model to explain the effects of fear on health attitudes and behaviors. It offers a useful insight to explain the variables that affect the adoption of sun protection behaviors [27]. According to PMT, environmental and personal factors can pose a potential health threat which includes two cognitive processes: threat appraisal and coping appraisal. Threat appraisal examines factors influencing the likelihood of engagement in potentially unhealthy behaviors, including [1] perceived internal and external rewards of unhealthy behavior; [2] vulnerability: a person’s belief that one is vulnerable to a health threat; and [3] perceived severity: one’s belief that a health threat is serious. Fear is an intermediate variable between perceived vulnerability and perceived severity by assessing the threat. Coping appraisal evaluates the ability to deal with a threat and includes [1] perceived self-efficacy: a person’s belief that she can successfully perform the suggested behavior; [2] perceived response efficacy: a person’s assessment that the proposed behavior is effective; and [3] perceived cost: one’s estimate of the costs associated with performing the protective behavior. These two cognitive-mediated evaluation processes are combined to form the needed motivation for protection. Thus, adapting to a healthy behavior is a transient process of turning motivation into intention and behavior [28, 29]. Masoudi et al. reported that an educational intervention based on the theory of protective motivation was effective in promoting boys’ knowledge and behaviors in preventing UV damage [30]. Also, Ch’ng and Glendon [31] investigated the effectiveness of the PMT variables as predictors of sun protection behaviors in adolescents. They found a relationship between protection motivation and observed behavior, so adolescents paid particular attention to preventive measures to minimize sun exposure side effects (Fig. 1).

**Fig. 1 Fig1:**
[figure not shown]
Constructs of PMT

### Objectives

The overall objective of the trial is to determine the effectiveness of combining the Sunshine and Skin Health and WhatsApp apps intervention to improve sun-safe and healthy behaviors based on the protection motivation theory (PMT) among primary school students.

More specifically, the study aims are to compare the control and intervention groups over time (before (T1) and immediately after the intervention (T2) and at the 3-month follow-up (T3)):

Sun protection behavior.PMT constructs including perceived vulnerability, perceived severity, response effectiveness, self-efficacy, reward, perceived response cost, fear, and protective motivation.

### Trial design

This randomized controlled trial (RCT) is an artificial intelligence technology-based education intervention with two-arm superiority parallel randomized controlled trial with a control group. The primary endpoint is the group difference in sun-protective behaviors and PMT constructs immediately after the intervention (T2). The secondary endpoint is the group difference in sun-protective behaviors and PMT constructs at 3-month follow-up (T3). Randomization will be performed using a 1:1 (control: intervention) ratio.

## Methods: participants, interventions, and outcomes

### Participants

Students in their fourth to sixth years of elementary school will be chosen as participants.

Inclusion criteria are as follows:From age 10 to12 years old (from the fourth to sixth grade of elementary school).Access to a smartphone, tablet, laptop, or computer.Access to the Internet and social networks (e.g., WhatsApp)

Exclusion criteria are as follows:Students who do not want to continue cooperation at any stage.Illness or disorder making it impossible to perform the intervention program.

### Description of study settings

This study is a randomized controlled trial (RCT) comparing intervention program with a control group in 10- to 12-year-old elementary school students. The project was implemented from April 2022 to July 2022. This period included participant recruitment, baseline data collection, and intervention (see Fig. 2). Randomization will be multi-stage random performed using a 1:1 (control: intervention) ratio. For this purpose, a list of elementary schools will be prepared. Thus, Zahedan city will be divided into five education districts and randomly selected four schools from each district (one girl’s and boy’s school as the intervention group and one girl’s and boy’s school as the control group). A self-administered questionnaire online will be provided to students through school information channels so that those who volunteer may participate in this research.

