**Fig. 2 Fig2:**
[figure not shown]
Trial diagram

After approval of the Ethics Committee in Research of Shahid Sadoughi University of Medical Sciences (IR.SSU.SPH.REC.1399.135), a letter will be sent to the General Department of Education in Zahedan Province to obtain all elementary school lists and permission to conduct the research. The researcher will hold coordination meetings with school principals and explain the research clearly. During the COVID-19 prevalence, a specific application (the SHAD web) was developed by the ministry of education to be used for all schools for teaching, parental involvement, and other activities. Each school has this application. After the schools’ agreement, an announcement of the study will be posted on the schools’ channels. Online self-administered questionnaire will be provided to the target group through these school information channels (the SHAD web). Also, students’ written consent (electronically) is obtained before completing the questionnaire and documented in the experimental database. In addition to the consent of the students, the consent of the parents is also required. Thus, a link to an electronic consent form will be sent to parents. Parents who have agreed to the participation of their children send an electronic consent form to the researcher. After reviewing eligibility criteria, eligible students will complete baseline measures and then will be randomly divided into two groups (control and intervention) as detailed above and below.

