### Randomization

The simple randomization will be done to assign participants for study groups by an independent statistician with a 1:1 allocation. A list of schools will be provided by referring to the Department of Education. Thus, Zahedan city will be divided into five education districts and randomly selected four schools from each district (one girl’s and boy’s school as the intervention group and one girl’s and boy’s school as the control group). A total of at least 20 elementary schools in Zahedan, with approximately 320 participants, will participate by simple randomization methodology. Once the students have consented and completed the baseline assessments, they will be randomized to intervention and control groups. From each school, the students selected will receive a special code through SPSS software, and after analyzing the data, they will be selected randomly through these codes. The independent statistician who has done the randomization informs the students by phone. Due to the nature of the intervention, it is impossible to blind participants and interventionists during the study. Still, outcome assessors will be blinded to group allocation in the final database as new identification numbers are assigned to participants. We will use the waiting-list control group design. After assessment T3, the control group will participate in the intervention program. This will be done so that both groups can experience the program. If participants withdrew or discontinued the educational intervention, researchers made efforts to encourage them to continue the study through two contacts. Also up to three text messages will be sent as reminders to complete questionnaires. Non-responders will be followed up by phone during the valuation period. Additionally, to increase adherence, digital notifications and reminders were sent to participants reminding them to visit and use the health messages, educational files, and skin cancer clip.

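### Schools are labelled intervention or control when selected, yet students are said to be randomised after baseline; if the label sets the arm, allocation precedes recruitment and differential volunteering can bias T2 and T3

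*Protocol article*

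**What the plan says.** The protocol article describes allocation in two ways.

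**By school.** Under Description of study settings, and again under Randomization, Zahedan is divided into five education districts and four schools are drawn in each: "one girl’s and boy’s school as the intervention group and one girl’s and boy’s school as the control group". The settings section presents this as the way the 1:1 randomisation is carried out.

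**By student.** Later in the settings section (after Fig. 2), "eligible students will complete baseline measures and then will be randomly divided into two groups (control and intervention) as detailed above and below". Under Randomization, "Once the students have consented and completed the baseline assessments, they will be randomized to intervention and control groups". The same section says "The simple randomization will be done to assign participants for study groups by an independent statistician with a 1:1 allocation", and that this statistician informs the students by phone. Under Questionnaires, T1 is placed before randomisation.

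**Recruitment.** The settings section gives these steps: "The researcher will hold coordination meetings with school principals and explain the research clearly"; once schools agree, "an announcement of the study will be posted on the schools’ channels"; the online questionnaire goes out through the school channels "so that those who volunteer may participate in this research". Child and parent consent electronically, and parents return their form to the researcher.

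**Blinding and outcomes.** Under Randomization, "it is impossible to blind participants and interventionists during the study", and controls receive the programme after T3. Behaviour and all the protection motivation constructs come from a self-administered questionnaire.

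**The concern.** The question is what can be known about a child's arm at the time that child is recruited. If a school is already an intervention or a control school when its principal is approached, every child there who has yet to volunteer has a settled arm. The researcher who explains the study and receives the consent forms could know it, and so could the principal. Families who expect the app now may volunteer in different numbers, or with different motivation, from families who expect to wait.

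The outcomes are self-reported motivation and behaviour, which are close to the traits that lead people to volunteer. An imbalance in readiness to change created at recruitment would be carried into the T2 and T3 comparisons. It need not show in the T1 score, so taking change from T1 may not remove it. A model with school effects would correct the standard error but not the imbalance.

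**Working it through.** **1. Does the school label set the arm?** The article points both ways.

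- *For the label:* the settings section introduces the school scheme as the randomisation procedure. The later sentence on dividing students refers to what is detailed above and below, and the scheme above it is the school labelling. If students were individually randomised within schools, calling a school intervention or control would have no function.
- *Against:* the settings, Randomization and Questionnaires sections all put randomisation after baseline, and Randomization says that participants are what the statistician assigns.

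The text cannot be settled without the sponsor.

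**2. What follows if it does?** Each district has one intervention and one control school per sex, so each district-by-sex pair is a block of two: one label reveals the other. All recruits in a school share one arm, fixed before they volunteer. Randomisation after consent then conceals nothing, because the label has already decided the outcome.

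**3. What follows if it does not?** A recruit's assignment does not exist before consent and baseline, and this bias cannot arise.

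**4. Illustration of size under the school reading.** The plan gives no figure for this bias and no volunteering rates, so the bias *d* is an assumption.

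Inputs:
- SDs 2.17 and 1.75, baseline mean 5.39, target relative difference 20%, 160 per arm (Sample size). The 160 is taken as given; this point does not depend on how it was derived.
- At least 20 schools and about 320 students (Randomization), so about 320/20 = 16 per school.
- ρ = 0.05 (Sample size). The article does not define it; it is assumed here to be the intraclass correlation.

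Steps:
- SD = √((2.17² + 1.75²)/2) = 1.97. Target = 0.20 × 5.39 = 1.08 points.
- Design effect = 1 + (16 − 1) × 0.05 = 1.75. Effective n per arm = 160/1.75 = 91.4.
- With no true effect, the probability of a significant two-sided 5% test is P(|Z + d/√(2/n)| > 1.96).

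| Assumed residual *d* | Points | Share of 1.08 target | n = 160, no clustering | n = 91.4, clustering allowed for |
|---|---|---|---|---|
| 0.1 SD | 0.20 | 18% | 0.145 | 0.104 |
| 0.2 SD | 0.39 | 37% | 0.432 | 0.272 |

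The last column shows that allowing for clustering lowers the error rate but does not restore 5%.

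**5. Is that range of *d* reasonable?** Suppose that children volunteer when a motivation trait exceeds a threshold, with assumed rates of 30% in one arm and 50% in the other. The mean trait among volunteers is φ(z)/p: 0.348/0.30 = 1.16 and 0.399/0.50 = 0.80, a difference of 0.36 SD. With an assumed trait–outcome correlation of 0.3 to 0.5, the outcome differs by 0.11 to 0.18 SD. The arm with *fewer* volunteers is the more selected, so more volunteering in intervention schools would, in this model, bias against the intervention. The sign is therefore open.

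**6. Limits of the illustration.** It carries *d* whole into the T2 comparison, so *d* must be read as what remains after T1 is taken into account. The threshold model describes a trait that T1 may partly capture. The correlation between T1 and T2 is not given, so the standard error of a baseline-adjusted analysis cannot be computed.

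**The case against.** A reader might infer that the assignment *is* known before consent. The article does not support that. It nowhere says that principals, recruiters or families are told the label; the only disclosure it describes is the statistician's phone call. It does not date the labelling against the meetings with principals beyond the order in which the steps are described. The sentence on blinding concerns conduct of the study, not recruitment. The article is condensed, and the announcement text and concealment procedure may be in the full protocol. This stands: the supportable statement is that the arm would be fixed, and could be known, before consent.

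It can also be said that the point depends wholly on the school being the unit, so that it is only a consequence of the contradiction over the unit of allocation. It does depend on that. It does not vanish when the contradiction is resolved, however: a sponsor who declared schools the unit and added a cluster analysis would still have allocation ahead of recruitment.

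Randomization also says that students from each school get codes and are chosen at random through them. If this means sampling from the volunteers, it could even out the numbers enrolled, but volunteers could still differ between arms in composition.

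Finally, the bias sizes come from no source in the article, a stable trait difference would partly show at T1, and the direction is unknown. All of this stands. Imbalances above the 0.11 to 0.18 SD of the threshold model, such as 0.3 SD, have no support even from that model and are not used here.

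**Conclusion.** The concern holds in conditional form. The article attaches the arm to the school at selection and also says that students are randomised after baseline; both cannot determine the arm. If the label does, allocation precedes volunteering and consent in an open, self-report trial, with no stated step that withholds the label. Recruitment bias in the T2 and T3 differences is then possible in either direction, and cluster analysis does not cure it. If students are randomised after baseline irrespective of school, there is no such bias.

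The size is unknown. The rates of about 10% to 27% with design effect 1.75, and 15% to 43% without clustering, show only what an assumed residual imbalance of 0.1 to 0.2 SD would do to a 5% test. They do not predict what happened in this trial.

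**What to change.** Reconcile Description of study settings with Randomization, and state one unit and one order of steps.

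- **If schools are the unit:** draw the four schools per district without arm labels. Post one identical announcement in all of them, saying that the school will start either now or after T3. Close consent and baseline in all paired schools. Only then should the independent statistician allocate within each district-by-sex pair, for all pairs at once, and release the result.
- **If students are the unit:** delete the school arm labels, so that the allocation after baseline is really concealed.
- **If recruitment is already complete**, as the past tense used for April to July 2022 in the settings section may suggest: report which order was followed and who knew the labels. If labels came first, state the risk of recruitment bias as a limitation.

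The cost is wording and the order of existing steps; the statistician, schools, channel and number of children stay the same. The downside is that intervention schools wait until baseline closes in their paired school, which should be short because recruitment is online.
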